##### Clinical decision support tool (adaptive order set)

Completion of a pre-visit questionnaire by patients will automatically generate a passive alert (best practice advisory) to PCPs. The alert will summarize the questionnaire responses and prompt the PCP to open an order set (Additional file 4). An electronic order set is a tool designed to streamline ordering and documentation in the clinical setting, with the goal of presenting the right information to the right person at the right time in the right point in the workflow [16]. The I-COPE order set was designed based on the American Geriatrics Society “Geriatrics At Your Fingertips” pain management chapter and the CDC guideline for prescribing opioids for chronic pain [6, 7]. The order set includes seven sections: self-management (patient education handouts on non-pharmacologic pain management strategies, exercises, assistive devices), referrals to other specialists, topical medications, oral non-opioid medications, medications for acute-on-chronic pain, opioid medications, and OUD. Each of these sections includes brief guidance and links to additional resources. Associated orders are customized and pre-filled. Three out of seven sections of the order set are designed to adapt to pre-visit patient questionnaire responses and data from the EHR. For instance, if a patient screens positive for depression or has a history of depression, the *antidepressants* group within the *oral non-opioid medications* section will open, nudging towards this medication class. Alternative versions of other sections exist for patients with advanced chronic kidney disease, opioid or benzodiazepine prescriptions, positive drug use screening results, and a previous diagnosis of OUD.

##### Shared decision-making tool (conversation tool)

The I-COPE conversation tool is a one-page document that lists evidence-based examples of pain management strategies for older adults (Additional file 5). The conversation tool supports shared decision-making by offering a visually compelling summary of available approaches in simple language [17]. It is intended to facilitate the conversation about treatment options between the patient and PCP at the time of the visit and mirrors the options available in the electronic order set.

#### I-COPE training/education

Prior to the launch of I-COPE at participating clinics, the new clinical workflows and tools are announced at a clinical operations meeting during which PCPs are informed about training opportunities and encouraged to participate. Electronic and printed tip sheets are provided for PCPs and staff members. Training options include (1) self-directed brief online videos walking through the I-COPE tools and general principles of older adult pain management and shared decision-making or 2) an 8-session Project ECHO® (Extension for Community Health Outcomes) series entitled Pain Management and OUD in Older Adults. The local version of Project ECHO® at the University of Chicago is ECHO-Chicago. Each session is an hour long and includes a 30-min didactic topic delivered by a content expert and two 15-min discussions of real-world cases brought by participating PCPs. Project ECHO® is an innovative workforce development model for expanding primary care capacity in underserved communities [18–21]. It uses videoconferencing technology to “telementor” community-based clinicians via didactic education, group problem-solving with actual cases brought by clinicians, and expert advice on implementing best practices [22]. These clinicians then become a “force multiplier” as they serve as local experts. Participating PCPs receive continuing medical education credits.

### Randomization

Due to potential study arm contamination from certain PCPs who work at multiple sites, the 32 ACCESS sites and 3 UCM sites were bundled into 22 units (19 ACCESS and three UCM). We then randomized the 22 units into five steps, stratified by affiliation (ACCESS vs UCM) to balance the number of PCPs from ACCESS and UCM sites within each step. We also minimized sequential imbalance across multiple site-level characteristics by including volume and percentages of racial groups such as White, Black, Hispanic, Asian, and others [23]. We chose the randomization with the smallest total imbalance score of the characteristics, in which each characteristic was rescaled into a standard normal distribution to be on the same scale. Clusters were numbered one through five and the allocation sequence was concealed until clusters were assigned. The I-COPE study biostatistician (co-author [name]) generated the allocation sequence.

### Implementation plan

For each step, preparation of participating clinical sites for I-COPE implementation includes general information sessions on I-COPE, online training materials for involved PCPs and staff, and in-clinic tip sheets. PCPs are recruited for voluntary participation in Project ECHO® ahead of implementation. Once launched, the I-COPE study staff provide support and identify workflow issues. Completion of assigned pre-visit questionnaires and acknowledgement of completed questionnaires are tracked to monitor implementation progress.

### Intervention outcomes

The RE-AIM framework will be used to assess the effectiveness of the implementation of I-COPE (Table 3) [24]. Effectiveness outcomes will include an increase in the variety of recommended pain treatments at the clinic and PCP level, decrease in prescribed higher-risk pain treatments (discontinuation or decrease in prescribed daily milligram equivalents of opioids and Beer’s criteria medications), and decreases in patient pain scores (% of patients with high initial pain scores (≥ 6) who experience a 30% reduction in scores) at 6 months (Table 3). Additional outcomes include measures of use (reach and adoption) of I-COPE tools by PCPs and clinics, specific safe opioid prescribing measures, and evaluation of Project ECHO® participants through pre- and post-surveys that include change in PCP knowledge, attitudes, and self-efficacy related to managing older adults with chronic pain, opioid use, and OUD (Table 3). Outcomes will be evaluated again at 12 months to assess sustainability.

**Table 3 Tab3:** RE-AIM framework implementation outcomes used to evaluate the ICOPE program implementation

Framework dimension	Outcome
Reach	• # and % of eligible patients who complete the pre-visit questionnaire • # and % of eligible PCPs who use the I-COPE order set • # and % of PCPs participating in ECHO-Chicago
Effectiveness	• Change in a variety of recommended pain treatments • Change in prescribing of higher-risk pain treatments (opioids and Beer’s criteria medications) • Change in pain scores o % with chronic pain diagnoses and high initial pain scores (≥ 6) who experience a 30% reduction in scores in 6 months • Change in safe opioid prescribing practices o Annual drug screens in a patient with chronic opioid use o Naloxone prescribing in patients with > 50 MME equivalents of opioids or OUD o Co-prescribing of opioids and benzodiazepines • Change in self-efficacy and practice behaviors for ECHO-Chicago participants
Adoption	• # and % of clinics who use the I-COPE Program
Implementation	• # and % of eligible patients who received all I-COPE tools (pre-visit questionnaire and order set use) • # and % of PCPs who participated in ECHO-Chicago and attended all eight sessions
Maintenance	• Outcomes listed above at 12 months

*Abbreviation: PCP* primary care providers, *ECHO-Chicago* Extension for Community Health Outcomes-Chicago, *MME* morphine milligram equivalents, *OUD* opioid use disorder, *I-COPE* Improving Chicago Older Adult Opioid and Pain Management Through Patient-centered Clinical Decision Support and Project ECHO®

### Data collection

#### Clinics

We will collect descriptive characteristics about clinical sites, including size (i.e., number of patients and visits per year); number of PCPs and staff; PCP characteristics, including sex, race, ethnicity, and years in practice; and clinical resources (e.g., integrated behavioral health). Data extracted from Epic® will be used to calculate the use of the I-COPE tools by PCPs.

#### Patients

We will obtain data on all eligible patients who receive care at study sites during the study period, which is defined as 6 months prior to launch at the step 1 clinical sites through 12 months after the step 5 launch. We will collect de-identified patient pre-visit questionnaire responses, data on patient characteristics (e.g., age, gender, race, ethnicity, insurance), diagnoses, pain scores, medications, referrals, other treatments, mental health assessments, and indicators of safe opioid prescribing (e.g., urine drug screens, naloxone scripts).

### Sample size

We calculated the sample size for the effectiveness outcome that had pre-intervention data, change in patient pain scores (% of patients with high initial pain scores (≥ 6) who experience a 30% reduction in scores) at 6 months, using the sample size calculation method for closed cohort (a special case of expanding cohort) by Hooper et al. [25] and Hooper and Bourke [26]. We estimated that there were an average of 26 PCPs and about 600 patients per step. We expect that at least 68% of older adults with pain scores ≥ 6 experiencing ≥ 30% pain score reduction due to the intervention. The total sample of 3040 eligible patients within 5 steps is needed to ensure at least 80% power to detect the difference of 10% at a one-sided significance level of 5%. Given a total of > 3400 patients with baseline pain score ≥ 6 in the 35 sites, the power becomes much larger. More detailed information is available in the Additional file 6.

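### A pool of just over 3400 patients against 3040 required raises power from 80% to at most about 84%, so the large reserve claimed under Sample size does not exist

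*Protocol article*

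**What the plan says.** The Sample size section sizes the trial on one effectiveness outcome, measured after six months: the percentage "of patients with high initial pain scores (≥ 6) who experience a 30% reduction in scores". The calculation follows a published closed-cohort method, which the section treats as a special case of the expanding cohort that the trial uses. Its inputs are:

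- "an average of 26 PCPs and about 600 patients per step";
- a response of "at least 68% of older adults with pain scores ≥ 6" under the intervention, and a difference of 10 points;
- a one-sided 5% significance level.

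Its result is: "The total sample of 3040 eligible patients within 5 steps is needed to ensure at least 80% power". It then notes that more than 3400 patients have a baseline pain score of at least 6 and concludes that "in the 35 sites, the power becomes much larger". No figure is given for that larger power. Further detail is referred to Additional file 6. The registration table under Administrative information repeats 3040 as the target sample size.

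**The concern.** A reader of the last power sentence will take it that the trial has a comfortable reserve. The two counts beside it do not support that: 3400 is only about an eighth more than 3040. The Randomization section fixes 22 units in five steps, so extra patients make clusters larger and add no clusters, which is the less efficient way to gain power.

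Two further features bear on the reserve. The count of more than 3400 is defined by a baseline score, while the outcome also needs a score at 6 months. And about 600 patients per step, taken over five steps, does not give 3400.

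The change in pain scores is one of the three primary outcomes in the registration table and the only outcome used for sizing. A wrong statement about its power affects how a null result would be read and how much loss of follow-up scores the trial is thought able to absorb.

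**Working it through.** **Inputs, all from Sample size unless noted.** Required N = 3040; power 80% (stated as a minimum); alpha 5% one-sided; difference 10 points with 68% under the intervention, so 58% under control by subtraction; available N = 3400 (stated as a lower limit); about 600 per step; 5 steps. The 22 units are from Randomization.

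**The plan's own figure.** An individually randomised comparison of 58% with 68%, one-sided 5% and 80% power, needs 288 per arm, 576 in total. Reaching 3040 implies a design effect of 3040/576 = 5.3. The correlations behind that are not in the article, so 3040 can be neither confirmed nor refuted. It is taken as given below.

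**Power at 3400.** For a fixed number of clusters, the variance of a cluster-period mean has a between-cluster part, which does not depend on cluster size m, and a within-cluster part proportional to 1/m. Enlarging m shrinks only the second part, so information grows at most in proportion to N. Hence

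power(N) ≤ Φ[(z₀.₉₅ + z₀.₈₀) × √(N/3040) − z₀.₉₅], for N above 3040.

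- z₀.₉₅ + z₀.₈₀ = 1.645 + 0.842 = 2.486
- √(3400/3040) = √1.118 = 1.058
- 2.486 × 1.0576 = 2.630
- Φ(2.630 − 1.645) = 83.8%

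This bound needs no correlation values.

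**Sensitivity.**

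- A closed-cohort stepped-wedge variance, anchored at 80% for 3040, was run over assumed values: intracluster correlation 0.001 to 0.2, cluster autocorrelation 0.5 to 1, individual autocorrelation 0 to 0.7, with 5, 22, 35 or 130 clusters, with and without a transition period. Power at 3400 is 80.0% to 83.8%.
- Reading the stated minimum power as 80.5% at 3040 gives 84.2% at 3400.
- Reading the available count as 3499 gives 84.7%; both readings together give 85.1%.
- Under the most favourable scaling, 90% power needs 3040 × [(1.645 + 1.282)/2.486]² ≈ 4211 patients.

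**Follow-up scores.** If 3040 means evaluable patients, 3040/3400 = 89.4% of the baseline pool must have a 6-month score. The documents give no follow-up rate, so the rates below are assumptions. When N falls below 3040, proportional scaling is the worst case, because with clustering the loss of information is less than proportional. The ranges use intracluster correlation 0.005 to 0.10, cluster autocorrelation 0.7 to 1.0, individual autocorrelation 0 to 0.7 and no transition period. The 130 clusters are 26 PCPs × 5 steps, also an assumption.

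| Share of 3400 with a 6-month score | N | Worst case | 22 clusters | 130 clusters |
|---|---|---|---|---|
| 80% | 2720 | 76.0% | 76.0–79.8% | 76.0–78.9% |
| 70% | 2380 | 71.1% | 71.1–79.4% | 71.1–77.4% |
| 50% | 1700 | 58.5% | 58.6–78.3% | 58.6–72.8% |

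**Counts.** 5 × 600 = 3000; 3040/5 = 608; 3400/5 = 680. The gap between 3000 and 3040 is 1.3%. The gap between 3000 and 3400 is 13.3%.

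**The case against.** The strongest reply is that the phrase is loose wording with no consequence: it changes neither the required number, the outcome nor the analysis, and all eligible patients at the sites are included anyway. That stands as an argument about severity. It does not make the statement correct.

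Other replies limit what may be concluded:

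- **The three counts contradict one another.** A reader might infer this, but 608 per step is fairly described as about 600, and required and available totals are meant to differ. Only 600 against 680 per step exceeds rounding. Even that is an unclear label, since the section does not say that both count the same patients.
- **Any realistic loss of 6-month scores takes the trial below 80%.** This is also tempting, but the documents do not support it. A loss of up to 10.6% from 3400 still leaves 3040. Both the 80% and the 3400 are stated as minimums. Study design describes an expanding cohort with continuous recruitment, so the baseline pool is not shown to be the final analysed number. An allowance for missing scores may be in Additional file 6, and its absence from the article is not an error.
- **The proportional-scaling figures are the expected power.** They are not. The fixed clusters that limit the gain above 3040 also soften the loss below it.
- **Calling the 3040 eligible patients opens the denominator to everyone in Table 2.** The surrounding sentences restrict the sizing outcome to scores of at least 6, so the intended group can be read from context. A clearer label would still help.

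**Conclusion.** The statement that power becomes much greater with the available patients is wrong as written. With 80% at 3040 and a fixed number of clusters, 3400 patients give at most about 84%, or about 85% on the most generous reading of both minimums. With non-negligible clustering the gain can be under one point. The conclusion rests only on the article's own figures and on the fact that information cannot grow faster than the number of patients; it does not depend on the correlations in Additional file 6.

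Whether the trial will fall below 80% is not established. It depends on the share of patients with a 6-month score, on further recruitment, and on what 3040 counts. The point needs correcting, but it does not threaten the design.

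**What to change.** Replace the closing power claim with a computed figure: at most about 84% if all 3400 are evaluable, or the exact value from the correlations actually used. Base it on the number expected, from existing EHR data, to have both a baseline score of at least 6 and a 6-month score. If power is shown for lower follow-up, give a range and mark proportional scaling as the worst case.

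State what each count refers to: the 600 per step, the 3040 (high initial score only, or high initial score with a 6-month score, and whether it includes an allowance for missing scores), and the 3400. If 600 and 3400 describe the same population, make them agree; 608 per step are needed and 680 would be available.

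The cost is a rewritten paragraph, one EHR count and a less favourable stated power. No patients are added, and the design and analysis do not change.

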### Data analysis

An intention-to-treat (ITT) analysis principle will be applied to all outcomes. For analyses of the effectiveness outcomes, we will use the blended exchangeable correlation structure [27] via generalized estimating equation (GEE) and generalized linear mixed-effects model (GLMM) to evaluate the intervention effect over 2 years since the beginning of the program implementation. For analyses of outcomes that require data collection provided by the intervention, such as reach, adoption, and implementation outcomes, we will provide basic descriptive statistics per clinical site per period and over all clinical sites and all periods. The study results will be released to the participating physicians, referring physicians, patients, and the general medical community.

## Discussion

### Expected impact/significance

Older adults disproportionately experience chronic pain and are vulnerable to adverse consequences of both undertreated pain and from pain treatments, including opioid use. However, limited evidence exists on how to implement optimal pain management for older adults in a primary care setting. This novel study will be one of the first to integrate patient-reported data on symptoms and preferences, a clinical decision support tool, and a shared decision-making tool for older adults with chronic pain, opioid use, and OUD. We also use a pragmatic design to test real-world implementation and effectiveness. The stepped-wedge design allows for a staged rollout across 35 clinical sites within two health systems and assessment of the effectiveness of the program in existing clinical practice while controlling for secular trends. I-COPE uses ECHO-Chicago to distribute knowledge to PCPs about the I-COPE components and geriatrics management principles for older adults with chronic pain, opioid use, and OUD. Our work suggests that ECHO-Chicago improves self-efficacy and practice behaviors in geriatrics competencies for urban medical PCPs [28–30]. While I-COPE targets older adults, given the ongoing issue of how to address chronic pain, opioid use, and OUD more broadly, we believe that the results of this study and the resulting tools will have potential application in other age ranges and populations.

### Limitations

Findings may not generalize to non-urban populations or in settings with less availability to resources such as those offered by ACCESS and UCM clinical sites (access to behavioral health, PCP access to education, etc.).

## Conclusions

The goal of this study is to determine whether the implementation of I-COPE will improve clinical care for Chicago’s older adults with chronic pain, opioid use, and OUD. The integration of patient-reported data on symptoms and preferences, clinical decision support tools and a shared decision-making tool is innovative. Our results will be generalizable to other clinics that care for urban older adults. Lessons learned from this study could add to the evidence for the necessary components to effectively improve management for older adults with chronic pain, opioid use, or opioid use disorder.

## Data Availability

The datasets used and/or analyzed during the current study will be made available from the corresponding author upon reasonable request.
